**Abstract:**

The purpose of this study is to investigate the effects of engaging in gardening and art activities on the psychological, social, and physiological characteristics of healthy women as revealed by psychometric assessments and blood pressure and heart rate readings.

**Background:**

There is a limited, but sufficient body of anecdotal and empirical evidence that suggests gardening (Kaplan 1973; Kidd and Brascamp 2002; Park et al 2009; Sommerfeld et al 2010; van den Berg and Custers 2011; Cipriani et al 2017; Soga et al 2017), walking in a park (Hartig et al 2003; Maller et al 2006; Taylor and Kuo 2009) or experiencing nature (Ulrich 1981; 1986; Kaplan 1995; Berman et al 2008; Howell et al 2011; Keniger et al 2013) and similar people-plant interactions are therapeutic. In recent times, it is widely reported in the popular media that activities like gardening and spending time in gardens and nature help reduce stress and contribute to healing (Phillips, 2011; Franklin, 2012; Andrews, 2013). Indeed, gardening or working in the yard is a popular pastime or hobby for millions of adult Americans, being slightly more so for men than women, according to the latest U.S. Department of Labor’s Time Use Survey (ATUS, 2003-2015).

Studies have suggested that visual art, and particularly art depicting scenes of nature, appear to reduce anxiety and stress experienced by patients in hospitals (Ulrich and Gilpin, 2003; Nanda et al., 2010; Ulrich 2009). Ulrich and Gilpin (2003) proposed that visual art in healthcare settings should contain images of flowers, the countryside, landscapes and/or waterscapes. Observed therapeutic benefits attributed to images of nature may link with attention restoration theory (Kaplan 1995) where engagement of directed attention leads to fatigue and natural environments or images of natural environments appear to promote replenishment or restoration of the ability for using directed attention.

While creative arts therapy research has historically been mostly qualitative in approach, there have been studies that have taken a quantitative approach and provided evidence suggesting that for cancer patients there can be therapeutic benefits. Based on systematic review of 11 studies by Uttley and colleagues (2015), there was notable heterogeneity in the data within the art therapy literature leading to inconclusive support for the positive clinical effects of art for individuals with a mental health condition. Studies analyzed tended to be of low quality with small study populations and limited randomized and controlled experimental designs. In contrast, meta-analysis of 13 studies conducted by Boehm and colleagues (2014) indicated significant improvements in levels of anxiety for breast cancer patients compared to controls following art-based interventions. Boehm and colleagues found that treatment effects for depression symptomatology and quality of life were not significant. Another systematic review conducted by Puetz and colleagues (2013) found small to moderate effects in response to music, art, and dance/ movement therapies with regard to psychological outcomes in cancer patients. The review included 27 randomized clinical trials encompassing 1576 cancer patients that had studied the impact of arts interventions on psychological outcomes in cancer patients. The review was performed following guidelines set forth in the Preferred Reporting Items for Systematic Reviews and Meta-Analyses. The analyses showed that pooled arts interventions of the studies revealed reduced anxiety, depression, and with concomitant improved patients’ quality of life. While the evidence of therapeutic benefits accruing from engagement in arts activities is not extensive, there is sufficient empirical support to warrant further investigation regarding the potential therapeutic benefits of this form of intervention.

This proposed study is a follow-on study to a gardening study conducted at Wilmot Gardens in 2015 (IRB 201400425). The previous study revealed therapeutic benefits for study participants in a gardening treatment group compared to a no treatment concurrent control group (unpublished data). In part, this proposed study is designed to follow the earlier gardening study, while improving and reducing potential for bias in the experimental design with the addition of an active concurrent control group, in the form of an arts program. This design model allows for statistical analyses of relative-effect estimates as compared to absolute-effect estimates.

The reasons for selecting an all women, wellness study population are several-fold. There are known cultural, societal and sex differences in the way males and females respond to interactions with plants, and these factors are reflected in part by known consumer patterns. For example, Japanese men were less favorable towards the presence of street-side flowers compared to trees than women (Todorova et al 2004). More women than men agreed with statements that gardening satisfaction is peace/tranquility and plants make me feel calmer/more relaxed in a study of attitudes towards plants and gardening (Relf et al 1992). Women exhibited a stronger flower color preference than men when purchasing geraniums (Behe et al 1999). In a study of images of natural environments versus urban settings, Ulrich and colleagues (1981) found significant sex differences in the responses of women and men with respect to positive affect and attentiveness. Both aspects of psychological status declined more when women viewed urban scenes than they did for men. In a study of garden centers and mass merchandisers, it was found that 85% of shoppers were female and 58% were between the ages of 25 and 55 (Yue and Behe 2009). According to the Society of American Florists, men spend more on floral gifts, and more men than women buy roses and floral arrangements valued above $30. In contrast, women buy a wider range of floral gifts at a lower cost, and more women than men buy less expensive loose or bunched flowers, floral arrangements, flowering plants and dish gardens (<http://www.safnow.org/>).

Additionally, there appears to be evidence for sex differences in stimulus processing in the brain, particularly with respect to responses to various stimuli including visual stimuli (Klein et al 2003; Wrase et al 2003; Smeets et al 2006; Garn et al 2009; Frank et al 2010) in a number of fMRI studies. We believe a study population of a single sex, in this case only women, will reduce experimental variability and increase the probability of detecting a biological effect of the experimental treatment (McCarthy et al 2012). Moreover, it may be that some of the best-documented benefits of working and interacting with plants align well with disorders known to be more prevalent in women such as depression, Multiple Sclerosis, Chronic Fatigue Syndrome and Celiac Disease. We do understand over the time course of the proposed experimental treatment, participants’ menstrual cycle may contribute to variability in the experimental results.

The objectives of this research are three-fold:

1. Ascertain if engaging in a group-based gardening program will differentially alter the mental health status and/or quality of life of healthy women compared to engaging in a group-based art program.
2. Determine if engaging in a group-based gardening program will differentially alter satisfaction with participation in discretionary social activities compared to engaging in a group-based art program.
3. Establish whether blood pressure and/or heart rate will change relative to involvement in a group-based gardening program compared to a group-based art program.

The hypotheses, listed below, will be tested with a well-defined wellness population of women as detailed in a later section of this protocol (see Participant Eligibility Criteria section below). Assessment of the effects of the group-based gardening activity (GA) or art activity (AA) on the experimental populations will take two approaches, the first being the use of wrist cuff blood pressure monitors on the participants to assess systolic and diastolic blood pressure and heart rate that may be improved as a consequence of experiencing the cumulative gardening or art programs and associated stimuli. The second approach will employ widely used and well-established self-reported psychometric assessment instruments that will capture information about the health and well-being of participants.

**Specific Aims:**

The project goal is a better understanding of how working with plants in an indoor gardening program compares with working with art media in an indoor art program with respect to mental health status, satisfaction with participation in social activities, and heart rate and blood pressure patterns. Specifically, this project seeks to determine whether engaging in GAs or AAs can influence overall quality of life of the participants in a wellness population of women, and elicit a physiological effect that can be revealed by changes in blood pressure and heart rate. Assessments will be employed to characterize additional psychometric parameters and determine how they may correlate with changes in blood pressure and heart rate.

Three hypotheses will be tested:

1. Engaging in a group-based gardening program will differentially alter the mental health status and/or quality of life of participants, as compared to engaging in a group-based art program.
2. Improvements in satisfaction with participation in discretionary social activities in the gardening group will parallel improvements observed in the art group.
3. Blood pressure and heart rate of participants will be reduced post-intervention for both the gardening and art groups.

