**Research Plan:**

**Experimental Design:** Up to 40 (20 in gardening group and 20 in art group) participants will be recruited to take part in a series of GAs or AAs in experimental treatment sessions to take place over a four to five week period when greenhouse conditions are environmentally favorable. The experiment is designed to test for effects of engaging in group-based gardening or art on blood pressure and heart rate; satisfaction with leisure interests and relationships with friends; mental health which includes dimensions of depression symptomatology, anxiety, stress and mood disorder status; and overall quality of life of the participants. The purpose of this follow-up study is to determine whether there is a difference in treatment response by comparing assessments between the art and gardening groups using both physiological metrics and psychosocial measurements from both groups.

**Participant Eligibility Criteria:** We will select participants from a pool of potential volunteers assembled from respondents to a variety of print and broadcast advertisements, and those expressing interest resulting from word-of-mouth awareness of the recruitment efforts for the study. The study will focus on a wellness population, with similar eligibility criteria as the gardening study conducted in 2015. Participants must be 26-49 years of age, premenopausal women, preferably not pregnant at the time of enrollment in the study, be a non-gardener and non-artist, nonsmoker, in good health and have the ability to participate in all aspects of the study including working with plants in the greenhouse and working with art media in a conference room. Additional eligibility criteria include not having allergies to plants, plant parts like pollen, or plant-based foods, not having an addiction to alcohol or to recreational drugs or prescription medications, not suffering from recurring pain, exhibiting an average BMI less than 32 (a BMI chart will be provided for reference), and not having been diagnosed with any diseases, disorders or disabilities that presently negatively affect daily life. A screening questionnaire has been developed to reveal these health-related criteria (see In-Person Eligibility Screening Questionnaire Gardening and Art Study).

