**Study Sample Size:** Based on a set of power calculations from the previous gardening pilot study (IRB201400425), we estimate needing up to 20 individuals in each of the experimental conditions, i.e. gardening program and art program. We will consider the study fully enrolled when 40 study participants are deemed eligible and ready to participate in the experimental intervention. Based on power calculations of psychometric data from the previous gardening study, minimum estimated sample sizes range from 12 to 17 participants required for the gardening experimental condition to achieve sufficient power. However, it is anticipated that perhaps as many as 50% of consented volunteers may fail one or more eligibility requirements, or elect not to continue in the experimental stage of the study.

We anticipate over the experimental treatment duration, that some participants might experience a life event (illness, loss of a loved one, serious accident or similar occurrences) that makes it necessary for them to withdraw from the study prior to study completion. Others may simply decide to cease participating. Some participants may miss some of the sessions. We believe the study, if fully populated, can sustain a 20% attrition rate in either of the two treatment groups and still provide valuable scientific information. Study staff will keep records of participant attendance. We have arbitrarily set an attendance minimum of 6/8 GA or AA sessions for the inclusion of data from a subject. Participants that have a major life event or miss more than two sessions will be allowed to attend all remaining gardening or art sessions. However, no further data from a subject will be collected following the third missed gardening or art session. Any collected data from such participants will be flagged and excluded from data analyses as determined to be scientifically appropriate.

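### Objective 2 asks whether gardening and art differ on social-activity satisfaction, but Hypothesis 2 predicts parallel improvement, and 20 per arm can support a similarity claim only within a wide margin

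*Protocol*

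**What the plan says.** The protocol puts the question about satisfaction with discretionary social activities (the SPDSA short form) in two ways.

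- **Objective 2** (end of Background): "Determine if engaging in a group-based gardening program will differentially alter satisfaction with participation in discretionary social activities", with the art program as comparator.
- **Hypothesis 2** (Specific Aims): "Improvements in satisfaction with participation in discretionary social activities in the gardening group will parallel improvements observed in the art group". The list it belongs to opens with "Three hypotheses will be tested".

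The Experimental Design paragraph of the Research Plan sides with the objective. It gives the purpose as to "determine whether there is a difference in treatment response by comparing assessments between the art and gardening groups", and it covers psychosocial as well as physiological measures.

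On size, the Study Sample Size paragraph says "we estimate needing up to 20 individuals in each of the experimental conditions, i.e. gardening program and art program", based on power calculations from the earlier gardening pilot. It adds that "minimum estimated sample sizes range from 12 to 17 participants required for the gardening experimental condition to achieve sufficient power" and that the study "can sustain a 20% attrition rate in either of the two treatment groups". According to Background, the pilot compared gardening with no treatment. SPDSA is collected before and after the program, at visits 2 and 11 (The Health and QOL Evaluations).

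**The concern.** A test of difference and a claim of similarity are different inferential tasks. A difference is shown when the confidence interval excludes zero. Similarity is shown when the interval lies inside a margin fixed beforehand. The protocol sets up the difference question for SPDSA and then lists the similarity prediction among the hypotheses to be tested.

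The risk lies in reading a null result. If the SPDSA comparison is non-significant, the wording of Hypothesis 2 makes it easy to report the prediction as confirmed, although a small trial often gives that result when the arms truly differ. The less precise the trial, the easier such a confirmation becomes. Nothing in the sample size paragraph links 20 per arm to showing that two active programs are alike.

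**Working it through.** **1. The passages side by side.** The outcome, arms and time frame are the same. Objective 2 and the study purpose look for a difference; Hypothesis 2 predicts matching improvement. Hypothesis 1 repeats the difference wording of Objective 1, so the change of wording between Objective 2 and Hypothesis 2 stands out.

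**2. Inputs.**
- From the protocol: n = 20 per arm; 20% attrition, so 20 × 0.8 = 16 per arm; a pilot minimum of 12 to 17.
- Not in the protocol, assumed here: two-sided 0.05; 80% power where a target is needed; equal SDs; differences in units of the between-participant SD of the score compared; equivalence by two one-sided tests (TOST) at 0.05 each with a true difference of zero; margins of 0.5 to 1.0 SD; correlation between visits 2 and 11 of 0.5 to 0.7 for the adjusted figures.

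**3. The protocol's own figure.** The 12 to 17 cannot be reproduced, because no alpha, power, effect or SD is given. Solving backwards at 80% power, it implies a difference of about 1.20 to 0.99 SD if these are per-arm sizes for a two-sample t-test, or about 0.89 to 0.72 SD if they are within-group (paired) sizes. Either way, the planning was for large effects.

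**4. Precision.** Half-width of the 95% interval = t(0.975, 2n−2) × √(2/n).
- n = 20: 2.024 × 0.316 = 0.64 SD
- n = 16: 2.042 × 0.354 = 0.72 SD

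**5. Chance that a real difference is non-significant** (noncentral t, noncentrality = d/√(2/n)).

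| True difference | 20 per arm | 16 per arm |
| --- | --- | --- |
| 0.3 SD | 85% | 87% |
| 0.5 SD | 66% | 72% |
| 0.8 SD | 31% | 41% |

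**6. Power of a formal equivalence test, unadjusted** (simulation). Success requires |difference| + t(0.95, 2n−2) × SE < margin.

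| Margin | 20 per arm | 16 per arm |
| --- | --- | --- |
| 0.5 SD | 3% | 1% |
| 0.8 SD | 60% | 43% |
| 1.0 SD | 86% | 74% |

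The 0.5 SD row is low because the 90% interval at 20 per arm already has an expected half-width of 1.686 × 0.316 = 0.53 SD, wider than the margin.

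**7. With baseline adjustment.** The residual SD is √(1−r²): 0.866 for r = 0.5 and 0.714 for r = 0.7, with one fewer degree of freedom. The margin stays in raw SD units.

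| Margin | 20 per arm, r = 0.5 / 0.7 | 16 per arm, r = 0.5 / 0.7 |
| --- | --- | --- |
| 0.5 SD | 14% / 40% | 5% / 24% |
| 0.8 SD | 78% / 93% | 64% / 85% |

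**8. Size needed for equivalence, unadjusted, 80% power.** n per arm = 2 × ((1.645 + 1.282)/margin)².
- 0.5 SD: 2 × (2.927/0.5)² = 68.5, so 69 completers
- 0.8 SD: 26.8, so 27
- 1.0 SD: 17.1, so 18

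**The case against.** Four points can fairly be made for the protocol.

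- **No rule is stated.** A reader might infer that the protocol will accept similarity from a non-significant test. It does not say so. It gives no test or interpretation rule for this hypothesis, and a margin could stand in an analysis plan that is not shown. This stands: the absence of a margin is not the finding. The opposition between Objective 2 and Hypothesis 2 remains whatever an analysis plan adds.
- **An objective asks and a hypothesis predicts.** Asking whether two programs differ and expecting that they do not is not illogical, so a null result is not strictly a failure of Objective 2. That is fair. But the prediction is listed for testing, and a test of difference cannot confirm it.
- ***Parallel* may only mean that both arms improve.** Hypothesis 3 is framed that way for blood pressure and heart rate. On this reading the equivalence figures do not apply. Hypothesis 2 would then be a statement about change within each arm, and would still not answer Objective 2.
- **The 3% figure is the unfavourable end.** SPDSA has a baseline value, and adjustment raises power. This stands, and the adjusted figures are given above. At a 0.5 SD margin power stays well below 80% over the assumed correlations.

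**Conclusion.** The inconsistency is in the protocol's own text and does not depend on any assumption. Its consequence is conditional: if *parallel* means similar, 20 per arm gives little support for it. The interval is about ±0.64 SD unadjusted (±0.72 SD at 16 per arm), a true 0.5 SD difference is missed about 66% of the time, and an equivalence test at 0.5 SD has about 3% power unadjusted or 14% to 40% adjusted. These sizes rest on the assumed alpha, SD units, margins and correlations.

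Two stronger conclusions do not follow. One is that no margin could be tested at this size: at 20 per arm, unadjusted power is 60% at 0.8 SD and 86% at 1.0 SD, and adjustment raises it. Such margins are wide, and whether they are acceptable on SPDSA is a judgement for which the protocol gives no figures. The other is that Hypothesis 2 fails because there is no untreated arm. Crediting within-arm improvement to the programs is a separate question, and rewording this hypothesis would not address it.

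This should be corrected before data are seen. It affects one named hypothesis, on one of six questionnaires, and not the trial as a whole.

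**What to change.** Restate Hypothesis 2 to match Objective 2: the gardening-minus-art difference in SPDSA at visit 11, adjusted for the visit 2 score, reported with a 95% confidence interval. Add one sentence saying that a non-significant difference will not be interpreted as equivalence.

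If the sponsor wishes to keep the similarity claim, the alternative is to align Objective 2 with it, define *parallel* through a prespecified margin on the SPDSA score, and state that 20 per arm can support only a wide margin.

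Either route is a matter of one to three sentences and changes nothing in recruitment, visits or instruments. The cost is scientific: the similarity claim is dropped under the first route and limited under the second.

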**Table 1. Sequence Timeline for the Eight Planned Experimental Gardening and Art Sessions.**

**Session Timeline**

| Timeline | Session Component |
| --- | --- |
| 0 min | Arrival and Sign-in/Pick up Name Tag |
| 0-10 min | Individuals Review Previous Activities (i.e. plant growth or art projects)/Instructors Greet Individuals and Assemble Group/Heart Rate and Blood Pressure Measurements Recorded |
| 10-20 min | Educational Module/Introduction to Activity/Demonstration of Activity as Warranted (booklet, instruction sheet, resource material handouts) |
| 20-50 min | Gardening or Art Activity, Questions |
| 50-70 min | Clean-up/Heart Rate and Blood Pressure Measurement Recorded/POMS and PSS Assessments (Even-numbered sessions) and BDI (Sessions 4 and 8)/Departure |
| 70-95 min | Session Review and Record Notes and Observations (Staff only) |

The GA sessions will be conducted inside the Wilmot Gardens 2700 sq. ft. greenhouse to increase control of and uniformity of environmental conditions compared to conducting sessions outside. Ambient environmental conditions for temperature and humidity in the greenhouse will be recorded at the beginning and end of each gardening session to provide information about the conditions over the duration of the gardening treatments. An evaporative cooling system and automated, adjustable shade cloth will be used to keep the greenhouse in a comfortable range for participants, and water fountains are located nearby for participants to keep hydrated throughout the sessions. Outside weather conditions during the scheduled gardening sessions will also be noted as sunny, overcast, rainy, hot or cold, low or high humidity. A restroom is readily accessible in the adjacent lobby of the greenhouse at the front of the structure. Art sessions will be conducted in the air-conditioned Wilmot Gardens Conference Center 1032 sq. ft. conference room that has the capacity to comfortably fit approximately 35 seated people or 10 art session participants and art materials and stands. The conference center is equipped with a kitchenette and accessible bathrooms.

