
**Data Collection:** The study team will collect baseline data on each subject prior to the beginning of the gardening or art activity sessions by administering various assessments during the orientation session, visit 2. In a final wrap-up session, visit 11, we will repeat the data collection, administering the complete battery of assessments following participation in the 8^th^ and final activity session of the program. Assessments of the participants will be in the form of self-administered health-related questionnaires, a discretionary social activities questionnaire, and heart rate and blood pressure monitoring. Trained research study staff will administer questionnaires. Heart rate monitoring for each participant will be accomplished for each session by way of BP wrist cuff readings and heart rate monitoring with the Omron 7 monitor (BP and HR) wearable. Two to three measurements will be taken at the beginning and at the end of each session.

**Other Study Procedures:** If a study participant completes a health and psychometric assessment instrument, and the study staff sees that their responses indicate depressive or anxiety symptomatology, the study staff will recommend that the individual seek professional help.

**Incidental Findings:** No incidental findings are anticipated, but if an incidental finding is made, the participant will be given a direct referral for medical follow-up. The results from the medical follow-up and review will not be provided by the service to the PI.

Anytime a health and psychometric assessment instrument is completed and the study staff sees responses that indicate depressive or anxiety symptomatology, the study staff will recommend the participant seek professional help. In the event that evaluation of the BDI-II or STAI responses suggests a risk of self-harm or suicidal behavior by a study participant, a qualified mental health professional arranged by the study staff irrespective of day and time will immediately evaluate the individual. Study staff will assist as needed to access emergency care at a recognized mental health treatment facility.

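### Hypothesis 3 predicts a fall in blood pressure and heart rate within both arms, which does not answer the between-arm Objective 3 and cannot be attributed to either programme

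*Protocol*

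**What the plan says.** The protocol's Specific Aims list three hypotheses to be tested. The third is "Blood pressure and heart rate of participants will be reduced post-intervention for both the gardening and art groups".

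Other parts of the protocol frame the question as a comparison of the arms:

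- Objective 3, at the end of the Background: "Establish whether blood pressure and/or heart rate will change relative to involvement in a group-based gardening program compared to a group-based art program".
- Research Plan, Experimental Design, where the purpose is to "determine whether there is a difference in treatment response by comparing assessments between the art and gardening groups", using physiological as well as psychosocial measures.
- Background, on the choice of design: "This design model allows for statistical analyses of relative-effect estimates as compared to absolute-effect estimates".

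The design improvement over the 2015 study is the "addition of an active concurrent control group, in the form of an arts program". The 2015 gardening group was set against untreated women: "compared to a no treatment concurrent control group (unpublished data". The present trial has no untreated arm. Every eligible woman is randomised to gardening or art, with up to 20 per arm.

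Blood pressure and heart rate are read at the start and end of visits 2 to 11 (The Health and QOL Evaluations). Visit 2 is the orientation and baseline visit, and visit 11 is the wrap-up.

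**The concern.** Objective 3 and Hypothesis 3 ask different questions. The objective needs a difference between two randomised groups. The hypothesis needs a fall from before to after in each group taken alone. If both arms fell by the same amount, Hypothesis 3 would be confirmed while the answer to Objective 3 would be no difference.

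Randomisation protects only the contrast between arms. A fall within an arm mixes any programme effect with everything else that changes between visit 2 and visit 11: familiarity with the wrist cuff, the staff and the site, regression to the mean, and season. By visit 11 each participant who has attended throughout has been measured at nine earlier visits, so habituation is a plausible source of drift in both arms.

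The protocol nevertheless reads such a fall causally. The Background describes blood pressure and heart rate as measures that the programmes may improve, and the Specific Aims speak of the activities producing a physiological effect. One of the three hypotheses could therefore be reported as supported, and taken as a benefit of both programmes, when neither had any effect.

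**Working it through.** **1. The statements side by side**

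| Place in the protocol | Comparison it calls for |
| --- | --- |
| Background, Objective 3 | gardening versus art |
| Research Plan, study purpose | gardening versus art, physiological measures included |
| Background, design rationale | relative rather than absolute effects |
| Specific Aims, Hypothesis 3 | after versus before, within each arm |

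Hypothesis 3 is the only one of the four that needs an absolute effect.

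**2. What each comparison estimates**

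Let D be the drift from visit 2 to visit 11 that would occur without any programme, and let G and A be the programme effects of gardening and art.

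- Expected change in the gardening arm: D + G
- Expected change in the art arm: D + A
- Difference between arms: (D + G) − (D + A) = G − A

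A drift common to both arms cancels from the difference and stays in each within-arm change. With no untreated arm nothing in the trial estimates D, so neither G nor A can be recovered separately.

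**3. How often a shared drift alone would support the hypothesis (illustration)**

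The protocol gives no blood pressure figures, and its sample-size statement rests on psychometric data, so there is no figure of its own to reproduce here. Inputs:

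- n = 20 per arm, from Study Sample Size, with everyone completing.
- Systolic SD 10 mmHg (assumed).
- Before-after correlation r = 0.5 to 0.7 (assumed).
- G = A = 0, and a shared drift of 3 or 5 mmHg (assumed).
- Paired t-test in each arm, two-sided 0.05 (assumed), counting only significant falls.

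SD of change = 10 × √(2(1 − r)), which is 10.0 mmHg at r = 0.5 and 7.75 mmHg at r = 0.7. The noncentrality is (drift / SD of change) × √20, on 19 degrees of freedom with critical value 2.093. The arms are independent given the drift, so the both-arms probability is the square of the one-arm probability.

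| Shared drift | r | Noncentrality | Significant fall, one arm | Both arms |
| --- | --- | --- | --- | --- |
| 3 mmHg | 0.5 | 1.342 | 24.7% | 6.1% |
| 3 mmHg | 0.7 | 1.732 | 37.6% | 14.2% |
| 5 mmHg | 0.5 | 2.236 | 56.5% | 31.9% |
| 5 mmHg | 0.7 | 2.887 | 78.2% | 61.1% |

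With no drift, the one-arm figure is 2.5% and the both-arms figure is 0.025² = 0.06%. The between-arm test rejects 5% of the time in every row, because the drift cancels.

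**4. Sensitivity to attrition**

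Study Sample Size tolerates 20% attrition per arm: 20 × 0.8 = 16. With n = 16, a 5 mmHg drift gives both arms 22% (r = 0.5) to 46% (r = 0.7), and a 3 mmHg drift gives 4% to 9%.

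All these figures are for systolic pressure alone. If diastolic pressure and heart rate must also fall in both arms, the probability cannot exceed the systolic figure and would usually be lower.

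**The case against.** Several points on the other side are fair.

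- *The two statements are compatible.* Both arms can fall and still differ. A reader might infer that Hypothesis 3 contradicts Objective 3, but the text shows only a mismatch: the hypothesis neither states nor answers the contrast in the objective. This stands.
- *The hypothesis can be tested as worded.* A reader might infer that the design cannot test it at all. A paired test in each arm is straightforward. What the design cannot do is attribute the fall to a programme, and the causal language elsewhere in the Background and Specific Aims is what makes that matter. This stands.
- *The randomised comparison is already planned.* The Specific Aims goal and the Experimental Design paragraph both compare the arms on physiological measures, so it would be wrong to infer that this comparison is lost. A statistical analysis plan, not shown here, may say which test serves which hypothesis. But the hypothesis is fixed in the protocol, and an analysis plan faithful to it would carry the same problem.
- *The measurement conditions are a lesser matter.* It is tempting to add that Table 1 states no rest before the opening readings, that "Two to three measurements will be taken at the beginning and at the end of each session", and that environmental recording is described for one setting only: "Ambient environmental conditions for temperature and humidity in the greenhouse will be recorded at the beginning and end of each gardening session". The first two are mostly procedural detail, and they apply to both arms. On the third, session readings are indeed taken in a greenhouse for one arm and an air-conditioned room for the other, so setting is tied to arm there. However, the greenhouse has evaporative cooling and shade control, and the protocol does not say where the visit 2 and visit 11 readings are taken. The documents therefore show no room confound for a visit 2 to visit 11 comparison.
- *The magnitudes rest on assumed values.* This is true, and the conclusion does not depend on them.

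**Conclusion.** The point holds as a mismatch of aims together with a within-arm claim that cannot be attributed to either programme. The protocol says its design supports relative effects, sets a between-arm objective, and then lists a hypothesis that needs absolute effects. That conclusion rests on the text alone.

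The percentages show only that the risk need not be negligible. They depend on the assumed SD, correlation and drift, refer to systolic pressure alone, and take all 20 women per arm as completers. They should not be read as the trial's false-positive rate.

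Severity: should be fixed. It concerns one of three hypotheses, and the randomised comparison remains intact. The correction changes what the trial may conclude about blood pressure and heart rate.

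**What to change.** Restate Hypothesis 3 as the between-arm difference, gardening versus art, in change in blood pressure and heart rate from visit 2 to visit 11, so that it matches Objective 3. Add that changes within each arm are descriptive and not attributable to the programmes, and bring the causal phrasing in the Background and Specific Aims into line.

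The cost is a few sentences of protocol wording. The drawback is that the trial gives up the claim that both programmes lower blood pressure and heart rate.

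Minor and optional: do not base the between-arm conclusion on session readings, because the setting differs by arm there, and take the visit 2 and visit 11 readings under the same conditions in both arms. This may need a little extra time or coordination at those two visits.
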